**13.4 Assessment of Adverse Event Outcome and Action(s) Taken**

The CI will follow every AE reported on the CRF to 1) a satisfactory outcome or stabilization of the event or 2) until the trial has ended. SAEs ongoing at the end of the trial will be followed by the CI for one additional month to determine an outcome, if possible.

The CI will record each AE outcome on the eCRF. The terms used to describe AE outcome are as follows (outcome of reaction/event at the time of last observation):

- Ongoing
- Resolved or stabilized without sequelae
- Resolved or stabilized with sequelae
- Death

Both actions taken in response to an AE and any follow-up results (including lab results) will be recorded in the subject's medical record in accordance with local procedure. Any treatment administered for the AE must be recorded in the subject's CRF. When subjects are discontinued from the study due to an AE, relevant clinical assessments and laboratory tests will be repeated as necessary until final resolution or stabilization occurs.

### **13.5 Reporting of Adverse Events**

In the screening phase, AEs will be reported if they begin or worsen from the time a subject signs informed consent for the Screening phase through 7 days after the last screening procedure and only if the investigator believes the event to be possibly associated with that study procedure.

In the MIT and Open-label follow-up phases, the study will capture AEs that begin or worsen in the period from provision of MIT informed consent through the either the last dose of study drug OR until discontinuation from the MIT (for those consented subjects who were never treated).

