#### **4.4.4 Open-Label Follow-up Phase**

After the completion of the 16-week randomized phase, patients will be offered open-label sildenafil for up to 1 year. Sites will maintain clinical outcome follow-up with these patients during this time, every 1-3 months, based on each site's standard practice. To preserve the scientific integrity of the MIT, all subjects will remain blinded to their MIT treatment assignment until after the MIT database is locked. In order to maintain the blind on a per subject basis and to minimize the possibility of sildenafil related adverse effects, at the beginning of the Open-label Follow-up Phase all patients will be down titrated from 80mg TID of sildenafil or placebo to 20 or 25mg of sildenafil TID. The doses will then be titrated upward as tolerated (see section 7.2 for dose adjustment guidelines in case of adverse effects). Doses will increase by 20-25mg TID every two weeks, but a faster dose escalation regimen will be allowed if, in the opinion of the treating clinician, a patient has become symptomatic due to apparent dose down-titration. The maximum dose will either be 75 mg or 80 mg TID, depending on 20 mg or 25 mg tablet availability. During the course of this year, the CI and administrative team will make every effort to assist patients in obtaining medication from a non-study source; this could include, for instance, helping obtain insurance coverage for their drug. Patients will be informed that these efforts do not guarantee availability of open label drug at the end of the study contract.

Adverse events and study drug dosing schedules will be collected during this open-label period.

If patients choose not to participate in the Open-Label Follow-up Study, they will be required to return to the clinic for a one-month safety follow-up visit approximately 30 days after the MIT Week 16 visit. Clinical Investigators will taper study drug for these non-continuing patients upon completion of the MIT treatment phase. The taper will continue for 3-7 days, based on CI judgment; blinded study medication will be provided in a quantity sufficient to supply the maximum taper period. Tapering is not recommended for patients requiring discontinuation of the drug due to AEs.

Refer to Chapter 13.3 of the MOO for a suggested taper regimen and for additional details.

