## **7 MONITORING OF SUBJECTS AND CRITERIA FOR WITHDRAWAL OF SUBJECTS**

### **7.1 Subject Discontinuation**

Therapy will be discontinued for the following reasons:

1. Major bleeding complication including intracerebral hemorrhage or stroke, GI hemorrhage, need for major surgery.
2. One episode of severe priapism defined as priapism lasting for more than 4 hours or requiring transfusion or surgical therapy (see Section 4.4.2.3 for further details of priapism monitoring)

3. Positive quantitative blood HCG or pregnancy
4. New retinal detachment, hemorrhage or clinically significant visual change (Subjects will be instructed by site personnel to alert their local CI of any visual changes between study visits; the CI will schedule an immediate evaluation by an ophthalmologist if a randomized subject complains of changes in vision.)
5. Serious adverse events considered to be related to the study drug
6. Introduction of specific treatments for pulmonary hypertension (excluding acute administration during a catheterization procedure to test vascular reactivity)
7. Initiation of chronic transfusion therapy (in this instance, EOS assessments should occur either immediately prior to initiation of transfusions or between 2-3 weeks after the transfusion)
8. Protease inhibitor treatment for HIV
9. If an emergency clinical unblinding of treatment assignment is required
10. Initiation of potent CYP3A4 inhibitor therapy (e.g., itraconazole, ritonavir, ketoconazole)

Sickle cell related clinical deterioration, other than those requiring initiation of chronic transfusion therapy, does not require withdrawal of study medication. Likewise, clinical deterioration of PH does not necessarily require discontinuation of study medication, unless the Investigator feels it is necessary to introduce another PH medication. In any situation where subject discontinuation is not required, the Investigator may always choose to discontinue the subject based on his or her clinical judgment. Any premature discontinuation of study drug precludes participation in the Open-Label Follow-up Phase of the MIT. At the time of study drug discontinuation all EOS visit assessments should be obtained to the extent possible. Such subjects should continue to be followed for adverse events and collection of other study data to the extent possible. Assessment of study endpoints should be made blinded to subjects' study treatment as much as possible.

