## **7.2 Dose Modification or Discontinuation Due to Expected Adverse Events: Headache or Facial/skin Edema**

Dose adjustment instructions for symptomatic/dose limiting headache or facial/skin edema sufficient to warrant discontinuation of the drug (only for symptoms that are severe enough as described by subject or physician to warrant holding the drug) are provided herein.

1. If present during initial dose (20 mg) hold for one day and rechallenge, if symptoms occur upon rechallenge discontinue drug. Data collection should continue for such subjects to the extent possible.

2. If present during dose escalation (40 or 80 mg) hold drug for one day and restart at previously tolerated dose for one week. If symptoms recur, discontinue drug but continue to follow subject for collection of safety and other data. If tolerated for one week increase dose to desired level as dictated by protocol. If symptoms recur upon second increase hold drug for one day and drop dose to previously tolerated dose for the duration of the trial.

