### **11.3 Safety Analyses**

All safety analyses will be performed using the ITT/SAF population. Safety variables will include laboratory variables and adverse event information. Specific endpoints that will be examined include:

- Incidence of AEs between baseline and Week 16
- Incidence of SAEs between baseline and Week 16
- Mortality incidence

The primary safety outcomes for the MIT will be all AEs; the subset of AEs defined as SAEs; and mortality. Treatment emergent AEs (those that begin or worsen after start of study drug), drug-related AEs, SAEs, and drug-related SAEs (as determined by the investigator) will be categorized by body system and MedDRA (Version 6.0 or later) preferred term.

The assessment of safety data will be based mainly on the tabulation of AEs, by TRV stratum and treatment arm. Additionally, AEs will be tabulated by severity and relationship to drug. Serious AEs will be described in detail. Comparisons across treatment groups, stratifying on TRV stratum will be made using a Cochran-Mantel-Haenszel chi-square test (or Fisher's Exact test as appropriate) on any AEs that occur in more than 10% of the subjects.

Additionally, continuous blood chemistry and hematology laboratory measurements will be categorized as normal/abnormal and summarized using shift tables, which describe changes in the values across visits.

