### **13.6 Reporting of Serious Adverse Events**

In the screening phase, SAEs will be reported if they begin or worsen from the time a subject signs informed consent for the Screening phase through 7 days after the last screening procedure and only if the investigator believes the event to be possibly associated with that study procedure.

SAE reporting during the MIT and Open-label follow-up phases will include events with onset dates occurring any time after the subject signs MIT informed consent until 1 month after the last dose of study drug or until discontinuation from the MIT (for those consented subjects who were never treated). All SAEs with onset prior to study discontinuation will be reported on the CRF and to the DCC Product Safety Team.

Sites will report SAEs to their IRBs according to section 13.7 and to that IRB's requirements.

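### Section 13.5 stops capturing non-serious AEs at the last dose, which does not fit the follow-up after stopping in 7.1 and 7.2 or the Week 16 AE incidence in 11.3

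*Protocol*

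**What the plan says.** Five parts of the protocol set or imply an AE window.

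- **13.5 (AE reporting).** In the MIT and open-label phases, AEs are captured if they begin or worsen from MIT consent "through the either the last dose of study drug OR until discontinuation from the MIT". The closing parenthesis confines the second limb to a special group: "for those consented subjects who were never treated".
- **13.6 (SAE reporting).** Serious events run longer: "until 1 month after the last dose of study drug or until discontinuation from the MIT", again with the second limb for never-treated subjects. A further sentence has all SAEs with onset before study discontinuation reported.
- **7.1 and 7.2 (stopping drug).** On subjects who stop early, 7.1 says: "Such subjects should continue to be followed for adverse events and collection of other study data to the extent possible". For recurrent headache or edema, 7.2 says: "discontinue drug but continue to follow subject for collection of safety and other data".
- **11.3 (safety analysis).** One of the listed endpoints is "Incidence of AEs between baseline and Week 16". It is analyzed in the ITT/SAF population, which 11.1 defines as all randomized subjects, classified by randomized arm whatever drug they took. All AEs are among the primary safety outcomes.
- **4.4.4 (end of the double-blind phase).** Completers who decline open-label treatment take a blinded taper of 3 to 7 days, and "they will be required to return to the clinic for a one-month safety follow-up visit approximately 30 days after the MIT Week 16 visit".

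**The concern.** For a treated subject, 13.5 ends capture of non-serious AEs at the last dose. A subject who stops early remains in the 11.3 denominator to Week 16, but new non-serious AEs after stopping are not recorded. The numerator and the denominator then cover different periods, and the shortfall grows with the proportion who stop and with how early they stop. If the arms stop at different rates, the comparison of a primary safety outcome shifts for a reason unrelated to harm. The semi-annual DSMB tables in 13.8.2 count subjects with or without an event, with no allowance for time observed, so they inherit the same problem.

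There is also an operational risk. One site may follow 7.1 and record these events while another follows 13.5 and does not. No analysis plan can recover events that were never entered.

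**Working it through.** The protocol gives no AE rate and no figure for this bias, so there is nothing to reproduce. The check has two parts.

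**1. Four subjects traced through the windows**

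| Subject | Event | 7.1 / 11.3 | 13.5 |
|---|---|---|---|
| Stops at Week 6, still followed | New non-serious AE at Week 9 | Inside | Outside |
| Stops at Week 6, still followed | AE began at Week 5, first mentioned at Week 10 | Inside | Inside (onset counts) |
| Completes, declines open label | New non-serious AE after taper, before the safety visit | After Week 16, but the visit exists for safety | Outside |
| Completes, enters open label | New AE in open label | After Week 16 | Inside (13.5 spans both phases) |

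If the taper starts at the Week 16 visit, the safety visit falls 30 − 7 = 23 to 30 − 3 = 27 days after the last dose. That interval is open for SAEs under 13.6 and closed for new non-serious AEs under 13.5.

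**2. Size of the effect on Week 16 incidence**

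Inputs:
- True 16-week incidence P, the same in both arms: assumed at 10%, 30%, 50% and 70%.
- Constant hazard λ = −ln(1 − P)/16 per week, and stopping independent of AEs: assumed.
- Proportion stopping, d. The protocol's section 11.6 scenarios are placebo 5% / sildenafil 2.5% and placebo 10% / sildenafil 5%. Both refer to stopping for clinical worsening or death only. The reversed rates used below are assumptions.

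Formulas:
- Observed incidence = (1 − d)·P + d·E[1 − exp(−λT)], with T the stopping time.
- Loss per stopper, L = P − E[1 − exp(−λT)].
- Sildenafil minus placebo = (d_placebo − d_sildenafil)·L.
- With T uniform on 0 to 16 weeks, L = P − 1 + P/(−ln(1 − P)).

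Example, P = 50%: L = 0.5 − 1 + 0.5/0.6931 = 0.221. At 10%/5% the difference is 0.05 × 0.221 = +1.11 points.

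Spurious difference, sildenafil minus placebo, in percentage points (column heads give placebo / sildenafil stopping):

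| P | 10% / 5%, even | 5% / 15%, even | 5% / 30%, even | 5% / 30%, all at Week 1 |
|---|---|---|---|---|
| 10% | +0.25 | −0.49 | −1.23 | −2.34 |
| 30% | +0.71 | −1.41 | −3.53 | −6.95 |
| 50% | +1.11 | −2.21 | −5.53 | −11.44 |
| 70% | +1.41 | −2.81 | −7.04 | −15.69 |

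Sensitivity to timing:
- At 10%/5% with all stopping at Week 1, the range is +0.47 to +3.14.
- At 5%/15% with all stopping at Week 6, L = P − [1 − (1 − P)^(6/16)]. This is 0.061 at P = 10% and 0.337 at P = 70%, so the difference is −0.6 to −3.4 points.

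For scale, the standard error of a difference with 66 per arm is √(2P(1 − P)/66): 5.2 points at P = 10%, 8.7 at 50% and 8.0 at 70%. A bias of 3.4 points at P = 70% is 3.4/8.0 ≈ 0.4 of a standard error.

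If capture ran to Week 16 for everyone, both arms would show P and the difference would be zero whatever the stopping rates.

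**The case against.** The other side has a good deal to say, and much of it limits the point.

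- **Onset, not detection, defines 13.5.** A reader might infer that anything first found after the last dose is lost, or that the 30-day visit yields no non-serious AE data. The text does not support that. AEs that began on drug are captured whenever they are reported, taper doses are study drug, and 13.4 has every recorded AE followed to outcome or stabilization, or until the trial ends. Only new onsets or worsenings after the last dose are lost.
- **Few subjects are affected.** Those who take drug to Week 16 are fully covered for the 11.3 endpoint. The AE that causes a stop is already counted, so that subject loses nothing for that term or for any-AE incidence.
- **Serious events are better protected.** 13.6 adds a month, and Table 4 separately documents hospitalizations, ED visits, transfusions, ACS and priapism.
- **7.1 is not absolute.** It says follow-up should continue as far as possible, so calling it a strict requirement goes too far.
- **The direction is open.** A reader might infer that sildenafil will look safer than it is. The 11.6 scenarios all have placebo losing more subjects, which would make sildenafil look slightly worse. Pre-marketing AE discontinuation was 2.5% against 2.3% (12.3.2.2). On the other hand, 7.2 stops for headache or edema could raise sildenafil stopping, and 2 of 22 sickle cell patients stopped for headache in an uncontrolled series (12.3.2.4).

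All of this stands. It reduces the size and removes any claim about direction. It does not reconcile 13.5 with 7.1, 7.2 and 11.3. On-treatment or exposure-adjusted tables may well be in the SAP, but they cannot supply post-stop events that were not collected.

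**Conclusion.** The inconsistency is real and should be corrected. Following 13.5 as written, the 11.3 endpoint cannot be measured as defined in subjects who stop early, because new non-serious AEs between the last dose and Week 16 are missing. The incidence is understated in both arms, and more in the arm that stops more. The documents do not establish which arm that will be.

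The likely size is small: 0.25 to 1.4 points at the protocol's 10%/5% rates and 0.5 to 2.8 points at an assumed 15%/5%, with stopping spread evenly. It reaches 7 points or more only with strong imbalance, such as 30% against 5%, combined with early stopping or high incidence. These figures assume equal constant hazards, stopping unrelated to AEs, and complete follow-up after stopping. The AE incidences are assumed throughout, and the protocol's stopping rates cover worsening or death only. The finding itself rests on the text and not on these figures.

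**What to change.** Amend 13.5 so that it agrees with 7.1, 7.2, 11.3 and 13.6:

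- In every randomized subject, capture all AEs that begin or worsen through the later of Week 16 or 30 days after the last dose, to the extent possible.
- For subjects who continue, keep the open-label AE capture that 13.5 already provides. Do not end capture at the first open-label dose; count events after that dose separately from the double-blind comparison.
- Report on-treatment AEs as a second table beside the Week 16 incidence.

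The cost is an amendment to 13.5, an edit to the CRF guide and a few more AE entries. Follow-up after stopping and the safety visit are already in the protocol. Because that visit may fall 23 to 27 days after the last taper dose, the amendment should say how the remaining days are covered, for example by a telephone contact, or accept the visit as the end of the window.

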### **13.6 Reporting of Serious Adverse Events**

In the screening phase, SAEs will be reported if they begin or worsen from the time a subject signs informed consent for the Screening phase through 7 days after the last screening procedure and only if the investigator believes the event to be possibly associated with that study procedure.

SAE reporting during the MIT and Open-label follow-up phases will include events with onset dates occurring any time after the subject signs MIT informed consent until 1 month after the last dose of study drug or until discontinuation from the MIT (for those consented subjects who were never treated). All SAEs with onset prior to study discontinuation will be reported on the CRF and to the DCC Product Safety Team.

Sites will report SAEs to their IRBs according to section 13.7 and to that IRB's requirements.

#### **13.6.1 Initial Reporting of SAEs by the Clinical Investigator (CI)**

After learning that a subject has experienced an SAE, the CI must report the SAE to the DCC Product Safety Associate by the end of the next business day. The CI will report the SAE to the governing IRB, according to section 13.7 and to that IRB's requirements.

The initial SAE report received from the site should include the following minimum information: the subject's study identification number; study treatment; the identification of the person making the report; the event, the CI's evaluation of the AE's relationship to study drug as well as 1) characterization (e.g., requires inpatient hospitalization > 4 days); 2) severity; 3) onset date; 4) outcome, if available; 5) actions taken; and 6) investigator comments.

The DCC Product Safety Associate will review the SAE Report, will gather additional information from the site, as necessary, and will consult with the medical monitor or his physician designee. Together, this Product Safety Team will determine 1) whether the SAE was expected and 2) whether the SAE was at least possibly related to the study drug. The Product Safety Team will also review the severity of the SAE in order to determine follow-up actions.

### **13.6.2 IND Safety Reporting to the FDA**

Because this study will be conducted under an IND, U.S. Government regulations 21CFR, Part 312.32 require the issuance of an IND Safety Report to the Food and Drug Administration (FDA) for all “serious” adverse events that are “unexpected” and for which there is a “reasonable possibility that the experience may have been caused by the drug.” Such serious events that are characterized as fatal or life-threatening must be reported to the FDA within 7 calendar days of the sponsor’s initial receipt of the information, whereas non-fatal and non-life threatening events must be reported within 15 calendar days.

The list in Table 11 identifies potentially serious adverse events that are “expected” based on the underlying disease, sickle cell anemia, or on the right heart catheterization procedure. Section 13.7.2 includes additional expected SAEs based on PH and study procedures. No expedited IND Safety Report is required if the event is considered to be expected based either on the sildenafil product label, the underlying disease states (i.e., PH or sickle cell disease), or the study procedures. Additionally, a serious adverse event requires an expedited report to the FDA only if it is considered to be at least possibly related to study drug.

The Product Safety Team will issue IND Safety Reports to NHLBI for all unexpected, serious adverse events that are believed to be at least possibly related to study drug. In compliance with FDA and National Institutes of Health (NIH) regulations, the Product Safety Team will prepare a collaborative report of these qualifying SAEs using the current version of the FDA MedWatch reporting form. The form will be sent to NHLBI for review and submission to the FDA. When an SAE requiring an IND Safety Report has not resolved by the report deadline, NHLBI will send the report to the FDA, and the Product Safety Team will work with the CI’s to gather follow-up reports on the event.

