**Table 2. Inhaled NO and Oral Sildenafil Challenge at Baseline**

|        | Intervention     | Duration           | Assessment                 |
|--------|-------------------------|---------------------------|-----------------------------------|
| Step 1 | Baseline                |                           | Resting hemodynamics              |
| Step 2 | Inhaled NO 40 ppm       | 10 minutes                | Resting hemodynamics  |
| Step 3 | None                    | 10 minutes                | Resting hemodynamics              |
| Step 4 | Sildenafil 60 mg orally | 30 minutes post oral dose | Resting hemodynamics              |
| Step 5 |                         | 60 minutes post oral dose | Resting hemodynamics              |

 Resting hemodynamics assessed at the end of the 10 minute period of inhaled NO, while the subject is still inhaling the NO.

Right heart catheterization will be repeated at the end of the double-blind phase. This hemodynamic assessment will follow the guidelines below:

- Subjects will take their nighttime dose of study medication, but will not take their morning dose prior to right heart catheterization.
- Subjects will bring study medication to visit.
- Study medication is administered with direct observation by study coordinator
- Right heart catheterization will be performed approximately 4 hours after study medication is administered
- Baseline hemodynamic measurements will be performed as outlined in Table 2 (steps 1-3).
- Blinded study medication will be administered and hemodynamic measurements will be performed at 30 and 60 minutes post dosing as outlined in steps 4 and 5 of Table 2.

If during right heart catheterization, it is not possible to obtain an adequate reading of the pulmonary capillary wedge pressure, a left heart catheterization will be performed for the measurement of left ventricular end-diastolic pressure.

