### **13.7.2 SAEs that Require Expedited Reporting to the IRB**

The following serious adverse events will be listed in the consent and reported to the local IRB within 7 days of a death or other life threatening event or 15 days of any other serious adverse event as outlined in the Interim Guidelines for Adverse Event Reporting. Other SAEs not noted herein will be reported to local IRBs per the guidelines of each IRB.

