#### **Pulmonary Artery Catheterization**

- Conduction abnormalities or atrial/ventricular arrhythmias occurring during cardiac catheterization requiring pacing or cardioversion/defibrillation.
- Injury to coronary artery, myocardium, or great vessel during diagnostic or research cardiac catheterization that requires further treatment; interventionally, surgically or pharmacologically.
- Pericardial effusion following diagnostic/research cardiac catheterization study requiring more intensive monitoring, or treatment such as a pericardial tap.
- Pneumothorax following diagnostic/research cardiac catheterization (left ventricular puncture) requiring more intensive monitoring or insertion of a chest tube.
- Hematoma with pseudoaneurysm (of major artery resulting from inadvertent puncture or of the pulmonary artery) following the catheterization.
- Apnea requiring airway management during conscious sedation for diagnostic cardiac catheterization.
- Myocardial infarction/neurological event during or following (within 24 hours) diagnostic/research cardiac catheterization

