#### **Hematology (Sickle Cell Anemia)**

- Priapism requiring medical or surgical intervention
- Acute chest syndrome/pneumonia requiring simple or exchange transfusion, admission and antibiotic therapy (not mechanical ventilation)
- Infections from bacteria, viruses, protozoa and fungi requiring vasopressor support or hospital admission
- Avascular necrosis of the femoral head requiring surgical intervention

- Bleeding requiring transfusion
- Major bleeding complication including intracerebral hemorrhage, stroke or GI bleed
- Sustained thrombocytopenia or neutropenia
- New leg ulcers requiring surgical intervention
- Greater than two admissions for vaso-occlusive crisis per week for two sequential weeks
- Retinal detachment or vitreous bleeding
- Pulmonary embolism
- All hospitalizations for medical indications (with the exception of hospitalizations for vaso-occlusive crises – per Section 13.7.1)

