## **13.8 Reporting of Serious Safety Issues to the DSMB; Suspension Guidelines**

Serious safety issues that arise in this study will be brought to the attention of the Data and Safety Monitoring Board (DSMB), which will make recommendations to the National Heart, Lung, and Blood Institute (NHLBI) regarding possible suspension or termination of the study. The NHLBI will consider the DSMB's recommendations, determine an appropriate action and notify the Data Coordinating Center (DCC). The DCC will notify all participating investigators, who will implement the actions directed by the NHLBI. This section defines "serious safety issues" and describes procedures for bringing them to the attention of the DSMB.

The DCC or PI will make the following types of reports that can alert the DSMB to a potential safety issue:

- Ad hoc reports of unexpected serious adverse events and those serious adverse events associated with major bleeding that are made within 7 or 15 calendar days, as specified in subsequent paragraphs.

- Reports of quarterly statistical analyses of all serious adverse events. The DCC will make such analyses quarterly, but files a report to the DSMB only when analyses indicate that a safety issue has arisen, as defined by the “alert” criteria.
- Reports of semi-annual DCC analyses of all adverse events and of adverse clinical laboratory trends. These reports will highlight any safety issues revealed by the analyses that meet the “alert” criteria.

The DCC will submit the DSMB report to the Chair of the DSMB Subcommittee appointed to monitor this study and to the NHLBI Project Officer and will submit the unexpected SAE report to all study investigators. Each CI will submit the unexpected SAE report to the local Institutional Review Board (IRB) and other local authorities in accordance with the institution’s regulations.

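### Section 13.6.2 uses an expedited-IRB list as a source of expected SAEs, so a possibly drug-related event after a catheterization-session dose can miss the FDA and DSMB case reports

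*Protocol*

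**What the plan says.** **Expectedness and the FDA.** Section 13.6.2 first gives Table 11 as the list of events expected from sickle cell disease or the catheterization procedure, then adds: "Section 13.7.2 includes additional expected SAEs based on PH and study procedures". Its exemption begins "No expedited IND Safety Report is required if the event is considered to be expected based either on the sildenafil product label" and goes on to cover the underlying disease states and the study procedures as equal grounds. Reports are issued as follows: "The Product Safety Team will issue IND Safety Reports to NHLBI for all unexpected, serious adverse events", with the further condition that the event is at least possibly related to study drug.

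**What Section 13.7.2 is for.** Its introduction says the listed events are to be "reported to the local IRB within 7 days of a death or other life threatening event or 15 days of any other serious adverse event". The items stand under four headings: catheterization, sickle cell hematology, pulmonary function testing and sildenafil. The catheterization items include "Myocardial infarction/neurological event during or following (within 24 hours) diagnostic/research cardiac catheterization". The hematology items include "All hospitalizations for medical indications", with an exception for vaso-occlusive crises.

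**DSMB.** Section 13.8 provides case-level reporting as "Ad hoc reports of unexpected serious adverse events and those serious adverse events associated with major bleeding". Table 12 agrees: all unexpected SAEs and all serious bleeding events are alerted. Other SAEs go through a quarterly Fisher exact test (Section 13.8.1), reported only at p < 0.01 with a higher rate on active treatment. There is also a semi-annual report of all adverse events (Section 13.8.2) and a safety report before each scheduled DSMB meeting (Section 13.10.1).

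**Drug at the catheterization.** Table 2, step 4, is "Sildenafil 60 mg orally" at baseline. At the end of the double-blind phase, blinded study medication takes its place.

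**The concern.** A list of events serious enough for rapid notice to IRBs is reused as a reason not to send rapid notice to the FDA. Once an event is expected, relatedness no longer matters for the IND report, because the event must be both unexpected and possibly related. The ad hoc DSMB report also depends on expectedness, except for bleeding.

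The catheterization session is where this matters most. It combines an invasive procedure, inhaled NO and an oral dose of sildenafil or study drug. Within the next 24 hours, timing alone cannot separate a procedure complication from a drug reaction. The wording allows the procedure explanation to settle the reporting question even when the drug explanation is judged possible.

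The scope of the cross-reference is also unclear. It speaks of events based on PH and on study procedures, but Section 13.7.2 has no PH heading. The Product Safety Team cannot tell from the text which items outside the procedure headings are meant.

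**Working it through.** The plan gives no figure to reproduce here, so the check traces the rules and then sizes the exposure and the fallback.

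**1. What is imported.** Items in Section 13.7.2 by heading: 7 catheterization + 12 hematology + 1 pulmonary function + 4 sildenafil = 24. Procedure items on any reading: 7 + 1 = 8. The other 16 depend on how the reference to PH is read.

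**2. Path of a myocardial infarction within 24 hours of a catheterization-session dose, judged possibly drug-related.**

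| Route | Condition in the protocol | Result if classed as procedure-expected |
|---|---|---|
| Notice to the DCC (13.6.1) | any SAE, end of next business day | made |
| Local IRB (13.7.2) | listed event, 7 or 15 days | made |
| IND Safety Report (13.6.2) | serious, unexpected, possibly related | not required |
| Ad hoc DSMB report (13.8, Table 12) | unexpected, or serious or major bleeding | not required |
| Quarterly DSMB report (13.8.1) | Fisher p < 0.01, active arm higher | only if the test alerts |
| Semi-annual and meeting reports (13.8.2, 13.10.1) | scheduled | included, later |

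**3. Sessions at which sildenafil is given.** Section 11.6 plans about 33 subjects per arm and TRV stratum, so 2 × 33 = 66 in the TRV ≥ 3.0 m/s stratum. All 66 receive 60 mg at baseline. At Week 16 only the 33 randomized to sildenafil receive it. Total: 66 + 33 = 99 before attrition. Subjects catheterized but then excluded on wedge pressure would add to the baseline count; the protocol does not say how many.

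**4. What the quarterly test needs.** Two-sided Fisher exact test, subjects as units, at the full 66 versus 66:
- 7 versus 0: p = 0.0132, no alert
- 8 versus 0: p = 0.0062, alert
- with 1 placebo case, 10 active cases are needed (p = 0.0087); with 2, 12 are needed (p = 0.0088)

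At 33 versus 33 (half enrollment, or the catheterized stratum alone), 7 versus 0 gives p = 0.011 and 8 versus 0 gives p = 0.0048.

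The alert probability is the sum of the two binomial probabilities over all tables with p < 0.01 and the active arm higher. Event rates are assumptions, since the protocol gives none. At 66 per arm it is about 2% for true rates of 5% versus 0%, 14% for 10% versus 2%, and 34% for 10% versus 0%.

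**5. Baseline dose.** The baseline catheterization precedes randomization (Section 4.4.2.4), and the challenge dose goes to everyone in the stratum. A table of treatment arm by occurrence cannot attribute a reaction to that dose, however many events occur.

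**The case against.** - **The cross-reference is qualified.** It is limited to PH and study procedures and says that Section 13.7.2 includes such events, not that every item is one. This stands. A reader might infer that the hospitalization line makes almost every hospitalized SAE expected. The text does not support that: the line is under sickle cell hematology, is confined to medical indications and excepts vaso-occlusive crises. Whether it is imported is unclear, and only that can be said.
- **Stroke keeps a DSMB case route.** Sections 7.1 and 13.7.2 both group stroke with major bleeding, and serious bleeding events are alerted individually within 15 days. This stands, so the gap at the DSMB concerns myocardial infarction and neurological events outside that group. The IND exemption is unaffected.
- **Some of these events may be expected anyway.** Section 12.3.2.3 describes myocardial infarction and cerebrovascular events in post-marketing experience, and Table 11 lists hemiplegia, seizure and silent infarct. The label is not at hand, so how many reports the cross-reference alone removes cannot be established. That limits the size of the effect but does not justify a procedure-based exemption for a possibly drug-related event.
- **People, not the list, decide.** The Product Safety Team, with the medical monitor, judges expectedness and relatedness for each SAE (Section 13.6.1). This also stands, which is why the event *can* miss the reports rather than must. Section 13.6.2 is nevertheless the written criterion they would apply.

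**Conclusion.** The defect is real but narrow. Section 13.6.2 takes expectedness from a list built for another purpose, and procedure-expectedness then overrides possible drug causation. At least 8 of 24 items are affected. The clearest is myocardial infarction or a neurological event within 24 hours of catheterization, at about 99 planned sildenafil sessions. Such an event can miss the IND Safety Report and, unless it counts as major bleeding, the ad hoc DSMB report. The quarterly test is a weak substitute, and for the baseline dose it cannot attribute a reaction at all.

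Two stronger readings should be resisted. A reader might conclude that rapid reporting to the FDA and DSMB is largely closed. It is not: SAEs outside the label, Table 11 and the imported items remain reportable, and each SAE is judged individually. A reader might also count two sessions for each of 66 subjects as drug exposures, but about half of the Week 16 sessions deliver placebo.

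The session count assumes the planned 33 per cell and no dropout. It counts opportunities, not misrouted reports, which the documents do not allow one to estimate.

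**What to change.** 1. Delete the sentence in Section 13.6.2 that makes Section 13.7.2 a source of expected SAEs, and state that listing in 13.7.2 does not make an event expected.
2. If PH- or procedure-expected terms are wanted, add them by name to Table 11.
3. State in Sections 13.6.2 and 13.8 that an SAE following a catheterization-session dose, and judged at least possibly related to that dose, is not exempt from IND and DSMB case reporting solely because it is a known procedure complication.

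A rule that every possibly related SAE be judged against the label alone is not needed. It would set aside the disease-expected terms in Table 11, which is a separate and debatable choice.

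The cost is about one paragraph of amended text and some additional 7- or 15-day reports. The documents do not allow their number to be estimated. Sample size, endpoints and visits are unchanged.
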